#### 2.12.2. Statistics

The primary outcome analysis will involve comparing the experimental group receiving CytoSorb^®^ with the control group receiving standard care (without CytoSorb^®^), focusing on the differences in the mean Inotropic Score (IS) at 72 h post-implantation. The primary analysis will encompass the full analysis set, including all patients who were randomized and received treatment, following the intent-to-treat (ITT) principle. Sensitivity analyses are planned in the per-protocol (PP) analysis set. A linear model will be fitted for the primary endpoint with treatment and baseline IS as fixed effects. The confirmatory analysis will be performed at a significance level of 5%. The mean difference of the primary endpoint will be estimated within the model and will be reported with 95% confidence interval. Categorical endpoints will be compared by Chi-square test/Fisher’s exact test between groups. According to the data distribution, two-sided independent samples *t* test or Mann–Whitney U test will be applied for continuous endpoints. Adequate descriptive statistics will be used to summarize the data in each group. All secondary analyses will be performed exploratively, i.e., without adjustment for multiplicity. Safety analyses will be run in the safety population to be defined in the protocol; these analyses will summarize and tabulate all observed safety events including a measure of uncertainty (i.e., 95% confidence intervals).

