### 2.7. Endpoints

#### 2.7.1. Primary Endpoint

The primary endpoint of the ECMOsorb trial is the mean difference of the Inotropic Score (IS) 72 h after randomization (implantation of CytoSorb^®^ or a normal ECMO tube) between the two study arms. The Inotropic Score is calculated as: dopamine dose [μg/kg/min] + dobutamine dose [μg/kg/min] + 100xepinephrine dose [μg/kg/min] + 100× norepinephrine [μg/kg/min].

The role of dopamine in the management of cardiogenic shock remains a topic of debate. It has been observed that the administration of dopamine is associated with an increased incidence of arrhythmic events and higher mortality rates among patients with cardiogenic shock [27,28]. As a result, dopamine is not included in the repertoire of inotropic agents and vasopressors employed for the treatment of acute heart failure at our study site.

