#### 2.7.2. Secondary Endpoints of the Study Are as Follows (Selection)

Duration of renal replacement therapy (continuous venovenous hemodialysis (CVVHD)), mechanical ventilation, ECMO therapy, inotropic/vasopressor treatment 7 and 30 days after the beginning of the intervention.

30–day mortality defined as mortality, in the hospital or anywhere after discharge, within 30 days after the beginning of the intervention.

Changes in mediators/markers of inflammation, myocardial damage, oxidative stress, myocardial wall stress, myocardial remodeling, kidney injury and kidney function at baseline, every 24 h during the intervention phase (up to 72 h) and on day 7 after the beginning of the intervention.

Length of stay in ICU and total length of hospital stay until discharge/transfer within 30 days after the beginning of the intervention.

Echocardiographic parameters of left and right ventricular function at baseline, every 24 h during the intervention phase (up to 72 h) and on day 7 after the beginning of the intervention.

Marker of hemolysis every 24 h under ECMO treatment (up to 72 h) after the beginning of the intervention.

Implantation of an active assist device or heart transplantation assessed on day 30 after the beginning of the intervention.

Simplified acute physiology score (SAPS) II, acute physiology and chronic health evaluation (APACHE) II; sequential organ failure assessment (SOFA) score at baseline, every 24 h during the intervention phase (up to 72 h) and on day 7 after the beginning of the intervention.

EQ–5D–3L questionnaire including EQ VAS (visual analogue scale), rehospitalization due to heart failure measured 30 days after the beginning of the intervention.

Neurological outcome: mRS (modified Rankin Scale), incidence of apoplexy, Glasgow Coma Scale (GCS), neuron-specific enolase (NSE), S–100, cerebral performance category (CPC), if clinically necessary and available: Computed tomography (head CT)/medianus somatosensory evoked potential (SEP) at baseline, every 24 h during the intervention phase (up to 72 h), on day 7 and on day 30 after the beginning of the intervention.

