### 2.12. Statistical Considerations and Methods

#### 2.12.1. Sample Size

Sample size calculation was conducted for the primary outcome of Inotropic Score (IS) at 72 h following CytoSorb^®^ or tube implantation. The estimated sample size is based on the standard deviation (SD) of the inotropic score after 72 h from our own VA–ECMO patient population (SD = 5.6). To detect a difference of 5 points in the IS score between both groups with a power of 80%, a total of 44 patients (21 per group) need to be analyzed (two-sided independent samples t test, α = 0.05). Considering an anticipated dropout rate of 20%, the trial aims to recruit 54 patients, with 27 patients assigned to each group.

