## 3. Discussion

Despite the growing utilization of ECMO in various life-threatening acute conditions [12,30,31,32], significant progress in the field of mechanical circulatory support and critical care, the rates of morbidity and mortality among ECMO patients continue to be alarmingly high [12]. The ICU mortality rate for our ECMO patients is approximately 80%.

The effectiveness of CytoSorb^®^ remains a subject of controversy [33]. Triple-blinded, randomized trials investigating the acute hemodynamic, echocardiographic, immunological, and cellular effects of VA-ECMO with the concurrent use of an adsorber to mitigate or potentially prevent an associated inflammatory response in patients with cardiogenic shock have not yet been conducted. ECMOsorb aims to assess the effectiveness of CytoSorb^®^ through a triple-blinded, randomized trial involving a larger cohort of patients with cardiogenic shock and VA-ECMO. The trial will focus on evaluating a clinical endpoint associated with hemodynamic improvement. Establishing efficacy would represent an initial evidence-based advancement for this challenging patient population that is often difficult to treat.

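### The primary model has no outcome value for patients who die before 72 h, so as written it compares patients alive at 72 h under an ITT label, and the stated sensitivity analysis does not examine this

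*Protocol article*

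**What the plan says.** Section 2.7.1 defines the primary endpoint as the "mean difference of the Inotropic Score (IS) 72 h after randomization" between the arms. The score adds the current doses of dopamine and dobutamine to 100 times those of epinephrine and norepinephrine.

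Section 2.12.2 fixes the analysis: "A linear model will be fitted for the primary endpoint with treatment and baseline IS as fixed effects". It describes the analysis set as "including all patients who were randomized and received treatment, following the intent-to-treat (ITT) principle". Section 2.13.1 likewise ties the full analysis set to intention to treat. The one sensitivity approach named is: "Sensitivity analyses are planned in the per-protocol (PP) analysis set".

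Section 2.12.1 distinguishes patients who must be analysed from patients recruited and bridges the gap with a loss allowance: "Considering an anticipated dropout rate of 20%, the trial aims to recruit 54 patients". Death is not mentioned there.

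Mortality appears as a secondary endpoint in section 2.7.2, counted "within 30 days after the beginning of the intervention". Under section 2.12.2 all secondary analyses are exploratory. On background risk, the Discussion says "The ICU mortality rate for our ECMO patients is approximately 80" per cent. Nowhere does the article give mortality by 72 h, or say what a patient who dies before 72 h contributes to the primary analysis.

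**The concern.** Three stated elements fit together only if there is a rule for early death: an outcome that exists only in the living, a linear model on that outcome, and an all-patients label. Fitted as described, the model leaves out everyone without a 72-h score. Being alive at 72 h is itself an outcome after randomisation that the device could influence, so the groups left to compare need no longer be alike.

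The direction of error depends on who dies. If the device led to more early deaths among the sickest patients, its survivors would have lower scores and it would look beneficial. If it kept such patients alive, they would raise its mean and hide a benefit. Entering the dead as receiving no drug would be worse, because zero is the best possible score.

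A per-protocol analysis cannot reveal this. It selects further on events after randomisation and still has no score for the dead.

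**Working it through.** **1. The plan's own figure.** Inputs from section 2.12.1: difference 5, SD 5.6, two-sided α 0.05, power 80%. For a two-sample t test with n per group the noncentrality is 5 / (5.6 × √(2/n)). Exact power is 78.6% at n = 20, 80.6% at 21 and 82.5% at 22. So 21 per group is the smallest sufficient number, and 21 / 0.8 = 26.25, rounded up to 27 per group, or 54 in all. The plan's recruitment target is reproduced. (The stated total of 44 to be analysed is not 2 × 21 = 42, but the 54 follows from 21 per group.)

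**2. What the allowance covers.** 27 × 0.8 = 21.6 patients per arm, just above the 21 needed. It therefore covers early deaths only if they are at most about 20% and nothing else is lost.

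**3. Equal early mortality: power only.** 72-h mortality is an assumption, since the article gives none. Survivors are 27 × (1 − mortality), rounded; power is from the formula in step 1.

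| Deaths by 72 h, each arm | Survivors per arm | Power for 5 points |
|---|---|---|
| 10% | 24 | 86% |
| 20% | 22 | 82% |
| 30% | 19 | 76% |
| 40% | 16 | 69% |
| 50% | 14 (from 13.5) | 62% |
| 60% | 11 | 51% |

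These figures keep SD 5.6 among survivors and ignore any gain from baseline adjustment, as the plan's own calculation does.

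**4. Unequal early mortality: bias.** The stated model (treatment plus baseline IS) was fitted by simulation to 72-h survivors only, with at least 6,000 trials per scenario. Assumptions: 27 per arm, SD 5.6, correlation 0.5 between baseline and 72-h IS, no device effect on IS, and deaths falling on patients with high latent severity. The correlation of severity with the 72-h IS that the patient would have had is varied. A negative difference favours the device.

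| Deaths control / device | Severity–IS correlation | Mean IS difference | Significant in device's favour (nominal 2.5%) |
|---|---|---|---|
| 20% / 20% and 30% / 30% | 0.5 and 0.8 | about 0 | 2.2% to 2.7% |
| 20% / 30% | 0.5 | −0.3 | 3.9% |
| 20% / 30% | 0.8 | −0.5 | 5.8% |
| 20% / 30% | 0.9 | −0.6 | about 7% |
| 20% / 40% | 0.5 | −0.6 | 5.7% |
| 20% / 40% | 0.8 | −1.1 | 11.4% |
| 20% / 40% | 0.9 | −1.2 | about 14% |
| 30% / 50% | 0.5 to 0.8 | −0.6 to −1.1 | 5.6% to 10.1% |
| 40% / 60% | 0.5 to 0.8 | −0.7 to −1.2 | 5.3% to 10.6% |

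With equal mortality the total type I error was 4.4% to 5.0%. Adjustment for baseline IS does not remove the bias, because baseline IS does not capture all of the severity that drives both death and the later score.

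**The case against.** The article condenses a fuller protocol, and handling of deaths is often left to that document or to the SAP. Nowhere does it say that deaths are excluded; a linear model could be fitted with assigned values; and naming a per-protocol analysis does not rule out others. All of this stands: the survivors-only reading is what the stated model does when no death rule is given, not an exclusion that the article announces. It does not dispose of the point, because the article itself fixes endpoint, model and ITT label for the confirmatory test, and those three do not agree without such a rule. If a rule exists elsewhere, citing it and correcting the label is quick.

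A reader might infer from the Discussion that most patients will be missing at 72 h. The documents do not support that. The 80% figure is for the site's ECMO patients over the whole ICU stay, and section 2.9 excludes several high-risk groups, such as prolonged resuscitation and shock beyond 12 h.

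A reader might also infer that the primary comparison is biased whatever happens, or that a harmful device would go unnoticed. Neither follows. The bias needs early mortality to differ between arms and to relate to IS, and no section predicts such a difference. Mortality is recorded at day 7 and day 30 (Table 1), so a large excess would be visible. What remains is that no stated rule ties the reading of the primary result to early deaths.

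**Conclusion.** The point holds in a limited form. As stated in sections 2.7.1 and 2.12.2, the primary analysis estimates an effect among patients alive at 72 h, under a label that promises all randomised and treated patients, and the stated sensitivity analysis does not test what that selection does.

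The size is conditional on assumed 72-h mortality. Equal mortality gives no bias and a loss of power. A 10-point excess of deaths on the device (30% versus 20%) gives about 0.3 to 0.6 points of false benefit, and a 20-point excess (40% versus 20%) about 0.6 to 1.2 points. That is 6% to 12% of the 5-point target (0.3/5 to 0.6/5) and 12% to 24% (0.6/5 to 1.2/5). The chance of a falsely significant benefit rises from 2.5% to about 4% to 7% and 6% to 14% respectively. These figures rest on severity–IS correlations of 0.5 to 0.9 and a baseline correlation of 0.5. The documents fix neither.

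**What to change.** - Keep the linear model, but label its estimate as the effect among patients alive at 72 h.
- Add, as lead sensitivity analysis ahead of per-protocol, a worst-rank analysis in all randomised patients: death before 72 h ranks below every observed score, survivors rank by IS, with adjustment for baseline IS (for example a proportional-odds model).
- State that deaths are never entered as zero dose.
- Report 72-h mortality by arm beside the primary result.
- State whether the 20% dropout allowance includes deaths.
- State that a primary benefit is read as unsupported if the worst-rank estimate points the other way.

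The cost is some wording, one extra analysis of data that the trial should already hold, and a somewhat stricter condition for claiming benefit. No extra patients are needed. Making the worst-rank composite the primary endpoint is a separate trade-off, since power can fall if the device does not affect early death, and it is not part of this fix.

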**General examination**							
Medical history, comorbidities ^∆^	X		X				
Physical examination ^∆^	X		X	X			
Prior/concomitant medication ^∆^	X		X	X			
Neurological exam (incl. mRS) ^∆^	X		X	X	X	X	X
Quality of Life (EQ -5D-3L including EQ VAS)						X	X
SCOREs (SAPS II, APACHE II, SOFA) ^∆^	X			X	X	X	
Adverse events/complications ^∆^				X *	X	X	X

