**Diagnostic procedures**							
12-lead surface ECG ^∆^	X		X	X	X		
TTE ^∆^	X		X	X	X	X	
Technical data from ECMO ^∆^	X			X	X	X	
Laboratory evaluation ^∆^	X		X	X	X	X	
Local blood chemistry ^∆^	X		X	X	X		
PAC–Hemodynamics ^∆^	X			X	X		
Measurement of parameters of hemodynamics ^∆^	X		X	X	X	X	
Measurement of mortality ^∆^	X					X	X
Measurement of duration of ECMO, ventilation, dialysis, inotropic therapy ^∆^	X			X	X	X	X
Measurement of the neurological outcome ^∆^	X			X	X	X	X
VA–ECMO Implantation	X			X			

^∆^ Data documentation from clinical routine (if available). * Recording of AEs/SAEs after implantation of CytoSorb® adsorber or ECMO tube, ^†^ device = either CytoSorb^®^ adsorber (= intervention group) or ECMO tube (= control group) via black box. ^1^ within the first 6 h after implantation of VA-ECMO, ^2^ changed every 24 h within the intervention of 72 h, V = visit, mRS = modified Rankin Scale, SAPS = Simplified Acute Physiology Score, APACHE = Acute Physiology And Chronic Health Evaluation, SOFA = sepsis-related/sequential organ failure assessment score, ECG = electrocardiography, TTE = transthoracic echocardiogram, ECMO = Extracorporeal membrane oxygenation, PAC = pulmonary artery catheterization, VAS = visual analogue scale, h = hours.

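### The stated comparison of 30-day mortality is unadjusted although severity scores are scheduled at baseline: a valid test, but one adjusted model would be a cheap, low-priority gain in precision

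*Protocol article*

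**What the plan says.** All references are to the protocol article.

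- **Test.** Section 2.12.2 states one rule for binary outcomes: "Categorical endpoints will be compared by Chi-square test" or Fisher's exact test between groups. It names no covariate. The same section does adjust the primary endpoint, with a linear model containing treatment and baseline Inotropic Score (IS).
- **Endpoint.** Section 2.7.2 defines the mortality endpoint as "mortality, in the hospital or anywhere after discharge, within 30 days after the beginning of the intervention". Section 2.12.2 does not mention mortality by name, but the definition makes it categorical.
- **Status.** Section 2.12.2: "All secondary analyses will be performed exploratively, i.e., without adjustment for multiplicity".
- **Severity scores.** Section 2.7.2 lists SAPS II, APACHE II and the "sequential organ failure assessment (SOFA) score at baseline", then daily to 72 h and on day 7. The Table 1 row "SCOREs (SAPS II, APACHE II, SOFA") has a mark at V0. It also carries the footnote symbol that stands for "Data documentation from clinical routine (if available").
- **Randomisation.** Section 2.13.1 describes central 1:1 block randomisation and names no stratification factor. Section 2.12.1 plans 54 patients, 27 per arm.
- **Mortality level.** Section 3: "The ICU mortality rate for our ECMO patients is approximately 80" per cent. The article gives no assumed 30-day rate and no mortality effect.

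**The concern.** Mortality has no baseline value of its own, so the approach used for the IS (adjusting for its own baseline) cannot be carried over. A general severity score is the natural substitute, and three are already scheduled at V0. The stated 2×2 comparison uses none of them.

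Two things are at stake. The first is precision: if the score predicts death, adjustment gives a tighter estimate and somewhat more power from the same 54 patients. The second is the reading of the estimate actually obtained. In a sample this small the arms can differ visibly in severity by chance, and an unadjusted risk difference carries that difference with it. Section 2.6.2 names mortality among the measures meant to support an advantage of the adsorber, so its estimate will be read next to the IS result even though it is exploratory.

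**Working it through.** **Inputs from the article:** 27 per arm; two-sided α = 0.05; about 80% ICU mortality at the site, used here as a stand-in for 30-day control mortality. **Assumptions:** treated mortality of 60% or 50%; a standard normal baseline score with AUC 0.71 or 0.78 for death (log-odds slope 0.8 or 1.2 per SD), or no prognostic value; no missing scores.

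**1. The plan's own figure.** The article states no power for mortality. The 27 per arm comes from the IS calculation. With a difference of 5 and SD 5.6, the two-sided t test needs 20.7, so 21 per arm. Then 42 / 0.8 = 52.5, which gives 54 when rounded up with equal arms. (The printed total of 44 is not 2 × 21 = 42. That is a separate matter and does not affect this point.)

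**2. Power of the planned mortality test.** The normal approximation is Φ[(|Δ| − 1.96·SE₀)/SE₁], with SE₀ = √(2·p̄(1−p̄)/27) and SE₁ = √((p₁(1−p₁)+p₂(1−p₂))/27).

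- 80% vs 60%: SE₀ = √(2×0.70×0.30/27) = 0.1247; SE₁ = √((0.16+0.24)/27) = 0.1217; (0.20 − 0.2444)/0.1217 = −0.365; power 36%.
- 80% vs 50%: SE₀ = √(2×0.65×0.35/27) = 0.1298; SE₁ = √((0.16+0.25)/27) = 0.1232; (0.30 − 0.2544)/0.1232 = 0.370; power 64%.

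Exact enumeration (Chi-square, switching to Fisher when an expected count is below 5) gives 37.6% and 65.7%.

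**3. Validity.** With 80% mortality in both arms, simulation rejects in 5.3–5.9% of trials for Chi-square and about 2% for Fisher. Chance imbalance is already covered by the error rate.

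**4. Size of chance imbalance.** The standard error of the between-arm difference in a standardised score is √(2/27) = 0.27 SD. P(|difference| > 0.3 SD) = 2[1 − Φ(0.3/0.272)] = 27%. P(|difference| > 0.5 SD) = 2[1 − Φ(0.5/0.272)] = 7%. With 80% mortality and no treatment effect, such gaps shift the raw mortality difference by:

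| Gap | AUC 0.71 | AUC 0.78 |
|---|---|---|
| 0.3 SD | 3.5 points | 4.7 points |
| 0.5 SD | 5.8 points | 7.9 points |

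**5. Power with adjustment by the recommended method.** Firth penalised likelihood-ratio test, treatment plus one score, 27 per arm, 2000 simulated trials per scenario (Monte Carlo error about 1 point):

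| Score | 80% vs 60%: planned → Firth | 80% vs 50%: planned → Firth |
|---|---|---|
| Uninformative | 37.7% → 35.2% (−2.5) | 66.0% → 64.1% (−1.9) |
| AUC 0.71 | 37.2% → 38.5% (+1.3) | 67.4% → 70.4% (+3.0) |
| AUC 0.78 | 37.2% → 42.0% (+4.8) | 66.6% → 74.6% (+8.0) |

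The Firth test's size was 2.9–4.9%. A second simulation of 1500 trials gave size 4.0–4.7% and changes of about −2, +2 to +4 and +4 to +8 points. Together the two give about +1 to +4 points at AUC 0.71 and +4 to +8 at AUC 0.78.

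**6. Precision of the estimate.** In the second simulation the standardised risk difference was about 7–9% less variable at AUC 0.71 and 11–12% at AUC 0.78. Some of that reduction comes from the penalty's own shrinkage, so the score's contribution is somewhat smaller.

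**The case against.** The strongest reply is that nothing here is wrong. An unadjusted 2×2 test of a randomised comparison is valid, mortality is secondary and exploratory, and a supportive adjusted model could stand in an analysis plan that is not shown. All of that is right, and it is why the point is one of efficiency. It remains a point because Section 2.12.2 states the method for categorical endpoints, and an analysis plan that follows the article would inherit it.

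Several stronger readings are tempting, and the documents do not support them:

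- *That the unadjusted comparison is biased or unsafe.* The null rejection rates in step 3 show otherwise. Imbalance affects how close one trial's estimate is to the truth, not the error rate.
- *That adjustment is a free gain.* The article gives no prognostic strength for any score. A weak score costs about 2 points of power.
- *That the scores will exist for every patient.* Table 1 marks them as routine data, if available. The planned test needs no covariate; the adjusted model does.
- *That the gain is larger.* An ordinary adjusted likelihood-ratio test shows 72% (AUC 0.71) and 76% (AUC 0.78) at 80% vs 50%, but its simulated size is 6.0% against 4.4% for the planned test. Part of that gap is therefore not real, and it is not the method proposed here.
- *That mortality decides how the trial is read.* The primary objective in Section 2.6.1 is haemodynamic, and the article gives mortality no such role.

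The objection also rightly notes how few survivors there may be: 54 × 0.20 = 10.8, so about 11 if the arms do not differ. That limits the model to one covariate and favours penalisation.

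**Conclusion.** The point holds as a cheap improvement of low priority. The stated mortality comparison is valid but leaves some precision unused, and it leaves chance severity differences in the estimate. The benefit is modest: about +1 to +4 power points at AUC 0.71, +4 to +8 at AUC 0.78, and a loss of about 2 if the score carries no information. In every scenario examined mortality stays below 80% power, so adjustment does not turn it into a confirmatory endpoint. The better argument for the change is the estimate: a 0.3 SD severity gap, with a 27% chance of arising, would move the raw difference by 3.5 to 4.7 points at those AUCs.

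These figures rest on assumed AUCs, on ICU mortality standing in for 30-day mortality, on assumed treated mortality of 60% or 50%, and on complete baseline scores. Missing scores would be expected to reduce the gain.

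**What to change.** For 30-day mortality, as an exploratory analysis:

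- Pre-specify a Firth logistic model with treatment and one baseline severity score. Choose SAPS II or APACHE II and record the choice before unblinding, so that it cannot be made after seeing results.
- Report the standardised risk difference with its 95% CI.
- State an arm-blind rule for missing baseline scores, so that no randomised and treated patient drops out of the comparison.
- Keep the Chi-square/Fisher result alongside.

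The cost is analysis wording only, on data already scheduled for collection. The downsides are the need for the missing-score rule and a possible slight loss of power if the chosen score turns out to be weak.

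### Serial secondary endpoints with a collected baseline are given two-sample tests chosen from the data; baseline adjustment on a pre-fixed scale would gain precision and a consistent effect measure

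*Protocol article*

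**What the plan says.** Section 2.12.2 of the protocol article adjusts the primary endpoint for its baseline: "A linear model will be fitted for the primary endpoint with treatment and baseline IS as fixed effects". For the other continuous endpoints it states: "According to the data distribution, two-sided independent samples *t* test or Mann–Whitney U test will be applied for continuous endpoints". It names no covariate, no repeated-measures term and no criterion for choosing between the two tests. It also declares: "All secondary analyses will be performed exploratively, i.e., without adjustment for multiplicity".

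Section 2.7.2 lists three groups of continuous secondary endpoints that have a baseline and serial follow-up:

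- Biomarkers, worded as changes: "Changes in mediators/markers of inflammation, myocardial damage, oxidative stress, myocardial wall stress, myocardial remodeling, kidney injury and kidney function at baseline, every 24 h", continuing to 72 h and day 7.
- Echocardiography, not worded as a change: "Echocardiographic parameters of left and right ventricular function at baseline, every 24 h during the intervention phase (up to 72 h) and on day 7".
- Severity scores, also not worded as a change, for example "sequential organ failure assessment (SOFA) score at baseline, every 24 h during the intervention phase (up to 72 h) and on day 7".

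Table 1 places the scores, echocardiography and laboratory evaluation at the baseline visit, during the intervention and at the day 7 visit. The same list in section 2.7.2 also holds durations of support and lengths of stay, which have no baseline value.

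**The concern.** The plan accepts baseline adjustment for the primary endpoint but does not extend it to secondary endpoints whose baseline is collected anyway. Neither a two-sample t test nor a Mann-Whitney test can take a covariate or use several visits jointly. In arms of this size, a chance imbalance at baseline in a marker or score passes straight into an unadjusted follow-up comparison.

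The choice of test is also left to the observed distribution. A t test addresses a difference in means. A Mann-Whitney test addresses a shift in ranks and yields no mean difference. The reported quantity could therefore differ from one marker to the next.

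These endpoints carry the mechanistic aim. Section 2.6.2 makes the mechanisms by which cytokine-driven SIRS and organ dysfunction are limited the main focus of the secondary objectives. Imprecise estimates without a common effect measure would weaken what the trial can say about them.

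**Working it through.** **The plan's own figure.** Section 2.12.1 gives a difference of 5, SD 5.6, two-sided alpha 0.05, 80% power and 21 per group. The standardised difference is 5/5.6 = 0.89. Exact t-test power (noncentral t) is 78.6% at 20 per arm and 80.6% at 21, so 21 per group is reproduced. The printed total of 44 is not 2 × 21 = 42; that is a separate matter and does not affect this point.

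**Assumed input.** The correlation r between baseline and follow-up is not in the documents. The range 0.3 to 0.7 is an assumption, as is equal variance at baseline and follow-up.

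**Formulas.** Variance of the treatment difference, relative to an unadjusted follow-up comparison (= 1):

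- baseline-adjusted: 1 − r²
- change score: 2(1 − r)
- adjusted relative to change score: (1 − r²) / [2(1 − r)] = (1 + r)/2, which is below 1 for every r below 1

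| r | Adjusted, 1 − r² | Change, 2(1 − r) | Adjusted / change, (1 + r)/2 | Unadjusted n per arm matching 21 adjusted, 21/(1 − r²) |
|---|---|---|---|---|
| 0.3 | 0.91 | 1.40 | 0.65 | 23.1 |
| 0.5 | 0.75 | 1.00 | 0.75 | 28.0 |
| 0.7 | 0.51 | 0.60 | 0.85 | 41.2 |

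A change score beats ignoring the baseline only when r exceeds 0.5, and it never beats adjustment.

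**Illustration in power.** Take 21 per arm and borrow the standardised difference of 0.89. Replace the SD by 5.6 × √(variance factor); for example, adjusted at r = 0.5 gives 5.6 × √0.75 = 4.85.

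| r | Unadjusted follow-up | Baseline-adjusted | Change score |
|---|---|---|---|
| 0.3 | 80.6% | 84.1% | 66.5% |
| 0.5 | 80.6% | 90.3% | 80.6% |
| 0.7 | 80.6% | 97.7% | 95.4% |

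This shows scale only. The effect size and the 21 per arm belong to the Inotropic Score at 72 h, and the documents forecast neither for any secondary endpoint. The small cost of estimating the baseline slope is ignored.

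**Does choosing the test from the data inflate type I error?** This was simulated with 21 per arm and 8,000 runs: a Shapiro-Wilk check at 5% in each arm, then the t test if both arms passed and Mann-Whitney otherwise. Rejection under no effect was 4.7% for normal, 5.3% for lognormal and 4.6% for exponential data. There is no material inflation at a nominal 5%.

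**The case against.** The strongest case against is that this is a preference for efficiency and not an error. Randomisation keeps the unadjusted comparisons valid, the simulated type I error stays near 5%, and no confirmatory claim rests on these analyses. All of that stands, and it limits the point to precision and effect measure.

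A reader might infer that the plan throws away the baseline everywhere. The documents do not support that. The biomarker endpoint is worded as changes, so its baseline is probably used through a change score, and the gain from adjustment must then be judged against that. At r = 0.7 the comparison is 0.51 against 0.60, not 0.51 against 1.

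A reader might also infer a separate test at every visit among survivors. Section 2.12.2 does not say this; it only names tests that cannot combine visits. Nor would a repeated-measures model settle the matter. The Discussion puts ICU mortality of the site's ECMO patients at about 80%, and a model using all available visits does not resolve truncation by death.

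Finally, a condensed article may leave endpoint-specific models to an analysis plan that is not shown. That is fair for detail. Here, however, the article states a method, and a baseline-adjusted model in the analysis plan would depart from it.

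The size also depends on an unknown r: at r = 0.3 the variance gain over an unadjusted comparison is only 9%.

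**Conclusion.** The point holds in a limited form. As written, echocardiography and SAPS II, APACHE II and SOFA would be compared without their collected baseline, and biomarkers at best by change score. Durations and lengths of stay are outside the point.

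Over the assumed range r = 0.3 to 0.7, adjustment removes 9% to 49% of the variance of an unadjusted follow-up comparison (1 − 0.91 to 1 − 0.51). Against a change score it removes 35% to 15% (1 − 0.65 to 1 − 0.85). These figures rest on the assumed correlations and on equal variances.

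The second loss is a consistent effect measure, because the test is picked from the data without a stated criterion. Neither loss implies excess false positives or touches the primary conclusion. The change is worth making because it improves a stated method at almost no cost.

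**What to change.** For each serial continuous endpoint with a baseline, replace the two-sample test by a linear model with arm and baseline value, or by a repeated-measures model with baseline, arm, visit and arm-by-visit. Fix the scale of each endpoint before unblinding, for example the log scale for skewed markers. Report the adjusted difference at 72 h with its 95% CI as the main contrast. The two-sample rule can remain for continuous endpoints that have no baseline.

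Add a sentence on deaths: the estimates concern patients alive and measured at that time, or they rest on a missing-at-random assumption. The model does not resolve truncation by death.

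The cost is slightly more modelling work and a few lines of text. Table 1 marks these data as documented from clinical routine where available, so the text should also say how a missing baseline value is handled. No new data are needed, and the confirmatory test is unchanged.
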